### Recruitment and sampling

Recruitment into KODY and into ‘*Caring Dads* standard’ program will occur through referrals from a range of services, including other programs within Kids First and Odyssey House Victoria and external services such as the statutory child protection service, and other Melbourne-based DV and AOD services.

Fathers entering KODY or ‘*Caring Dads* standard’ programs will be assessed and invited at intake by program staff to participate in the evaluation, as will men’s (ex)partners. Researchers will follow up with interested participants to obtain informed consent which will be confirmed at each stage of data collection. Program staff will be consulted regarding any possible safety issues.

Three KODY groups and three ‘*Caring Dads* standard’ groups are planned for each year of the study, each with up to 10 participants. Assuming a medium effect size (based on Cohen’s d), a power of 0.80 and a two-tailed test across independent groups, this study will need to involve reports from 128 mothers, 64 in each of the KODY and comparison groups. Reported participation rates for evaluations of *Caring Dads* programs range from 62% [3] to 97% [5]. Assuming a partner contact success rate of 75% based on the benefits of the *Kids in Focus* program for women and children, this study will need to enrol 170 families across groups.

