Victorian domestic homicide reviews indicate that between 50–60% of murders occur in the context of the use of alcohol or other drugs [8] suggesting an association between the severity of DV and the use of AOD. In longitudinal studies, AOD use has emerged as one of few consistent predictors of men’s continued use of, or desistance from violence [9, 10]. Substance use is also associated with negative, hostile and aggressive parenting [11, 12]. The Australian *Caring Dads* evaluation for fathers who use violence found that a third of participants were accessing AOD services [6]. Some groups are over-represented in their need for these services. A significant proportion of the *Kids in Focus* clients at Odyssey House Victoria come from Aboriginal or culturally and linguistically diverse (CALD) backgrounds. In addition, a considerable number of men display co-occurring mental health issues [13]. Unemployed men who hold highly traditional notions of masculinity are also over-represented among users of harmful alcohol use and DV [10, 14, 15]. This body of research suggests the need to explore models of intervention that address both men’s substance use and their use of violence and coercive control [12].

There is widespread recognition that DV is predominantly a gendered issue of men’s violence towards women [2]. However, less attention has been given to children as victims of the destructive parenting behaviours of fathers who use domestic violence and coercive control [16]. The evidence is compelling and well established that children’s exposure has negative consequences for them [17]. These include adverse health impacts [18], the undermining of children’s emotional and psychological wellbeing [19], and problems connected with damaging behaviours. Similarly, the destructive impact for children living with parental harmful substance use is a significant driver of children into child protection and out of home care [20], particularly when there is co-occurrence with DV and carer mental ill-health [21, 22].

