### Eligibility criteria

The target group for study is fathers who use DV and AOD. Fathers and their (ex)partners eligible to participate in either the trial or the comparison programs will be eligible for the study. In both groups, eligible fathers must have contact with at least one child, be able to understand and speak English, and have capacity to maintain participation and attend group work regularly, bearing in mind their substance use status. Mothers participating in trial and comparison programs are also eligible for the study.

The trial program (KODY) will constitute fathers referred for their problematic AOD use and identified by AOD case managers as using DV, or at risk of using DV. KODY fathers must be receiving support through Odyssey House Victoria clinicians. These men, their children with whom they have contact, and the children’s mothers, will be offered support through *Kids in Focus* as part of the intervention group. The comparison group will comprise fathers who are referred (or self-refer) to a ‘*Caring Dads* standard’ program. These fathers will have been identified as using DV or being at risk of using DV.

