### Data analysis

Intent to treat analyses will be used so that all service users are included in the primary analysis, allowing for variations in levels of participation in KODY and including those who drop out prematurely. Assuming differences between groups, supplementary analyses will examine the extent to which intervention effects vary according to whether families received a higher or lower ‘dose’ of expanded service. Recognizing that fathers are not being randomly assigned to the intervention and comparison group, care will be taken to compare time 1 characteristics of groups and, if necessary, use propensity analyses in post-group and follow-up comparisons. Each component of the study will be analysed separately in the first instance, then brought together to triangulate data collection and analysis, before a final synthesis.

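### The 64 + 64 mothers and power of 0.80 hold only for an unadjusted comparison; the propensity-adjusted comparison that the entry rules make likely has no stated power and, without a gain from baseline scores, has less than 0.80

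*Protocol article*

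**What the plan says.** Recruitment and sampling sets the size of the study. It begins "Assuming a medium effect size" on Cohen's scale, sets power at 0.80, and reads on: "a two-tailed test across independent groups, this study will need to involve reports from 128 mothers, 64 in each of the KODY and comparison groups". The only inflation is for a 75% partner contact rate, which leads to 170 families.

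Data analysis acknowledges that fathers are not randomly assigned. It says that time 1 (T1) characteristics will be compared and that the team will, "if necessary, use propensity analyses in post-group and follow-up comparisons". It does not say whether this means matching, weighting or score adjustment.

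Eligibility criteria gives the two arms different entry rules. KODY takes fathers referred for problematic AOD use, and "KODY fathers must be receiving support through Odyssey House Victoria clinicians". Comparison fathers need only have been identified as using domestic violence or being at risk of it. The same section describes the study's target group as fathers with both problems.

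Background gives the article's only AOD figure for a Caring Dads population: an earlier Australian evaluation "found that a third of participants were accessing AOD services".

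**The concern.** The power figure belongs to one comparison and the bias-controlled analysis may be another. The t-test formula counts all 64 comparison mothers at full weight. A propensity method that balances AOD status gives little or no weight to comparison families whose father has no AOD problem, because they have no KODY counterpart.

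AOD status is hard to leave out of a propensity model here. It is built into the entry rule for one arm only, and Secondary outcomes and measures itself says that combined violence and substance use goes with more severe abuse, which is what the women's primary outcome measures.

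At stake is how a null result is read. A reader who sees 0.80 in the protocol may take a null adjusted comparison as a well-powered negative about a program meant to improve women's and children's safety. The Discussion does warn of limited power, but attributes it to small early samples and does not mention loss from adjustment.

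**Working it through.** **Inputs.** From Recruitment and sampling: medium effect, power 0.80, two-tailed, 64 per arm, 75% contact. Assumed: d = 0.5 and two-sided alpha 0.05, neither of which is printed. From Eligibility criteria: AOD share 1.0 in KODY and no fixed share in the comparison arm. Let q be the share of comparison fathers who are AOD-involved in the way KODY fathers are. The documents do not give q, so it is varied.

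**Step 1: the plan's own figure.** For a two-sample t-test the noncentrality is d / √(1/n₁ + 1/n₀). Power 0.80 needs 63.77 per arm, so 64. With 64 + 64 the noncentrality is 0.5 / √(2/64) = 2.83 and power is 0.801. A one-sided test would need about 50 per arm, so the printed figure is the two-sided one. Enrolment is 128 / 0.75 = 170.7, in line with the printed 170. The plan's figures reproduce.

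**Step 2: balance AOD status only, no baseline score, q = 1/3.** About 64 × 1/3 = 21.3 comparison mothers then carry the information.
- Weighting to KODY (64 v 21.3): noncentrality 0.5 / √(1/64 + 3/64) = 2.00, power 0.51.
- AOD as a covariate: the squared correlation between arm and AOD is (1 − q)/(1 + q) = 0.50, so the variance is multiplied by 1/(1 − 0.50) = 2. That leaves about 32 per arm effective and power 0.50, in effect the weighting result.
- 1:1 matching (21.3 v 21.3): noncentrality 0.5 / √(2/21.3) = 1.63, power 0.36.

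**Step 3: vary q, still without the baseline score.**

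| AOD share q in comparison arm | Weighting | 1:1 matching |
|---|---|---|
| 20% | 0.36 | 0.23 |
| 33% | 0.51 | 0.36 |
| 50% | 0.63 | 0.50 |
| 67% | 0.71 | 0.63 |
| 80% | 0.75 | 0.71 |
| 90% | 0.78 | 0.76 |
| 100% | 0.80 | 0.80 |

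**Step 4: add the T1 outcome score.** With correlation r between T1 and follow-up, the residual SD shrinks and the effective standardised effect becomes 0.5 / √(1 − r²): 0.577 at r = 0.5, 0.625 at r = 0.6 and 0.700 at r = 0.7. The documents give no r. Weighted power is:

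| q | r = 0 | r = 0.5 | r = 0.6 | r = 0.7 |
|---|---|---|---|---|
| 33% | 0.51 | 0.63 | 0.70 | 0.79 |
| 50% | 0.63 | 0.75 | 0.82 | 0.89 |
| 67% | 0.71 | 0.83 | 0.88 | 0.94 |

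Matching at q = 1/3 gives 0.45 (r = 0.5) and 0.61 (r = 0.7).

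**Step 5: could enrolment absorb the loss?** At q = 1/3, weighting without the T1 score needs about 128 mothers per arm, or 256. Planned capacity is 3 groups × 10 fathers × 3 years = 90 fathers per arm, 180 in all, or 180 × 0.75 = 135 mothers. Enrolment cannot make up the difference, so the remedy has to lie in the analysis and in what is stated.

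**The case against.** - **The calculation is right as printed.** This stands. The article names an independent-groups test, and 128 follows from it. A reader might infer that the sample size is miscalculated; it is not.
- **The propensity analysis is conditional and its form is open.** This stands. It is not a fixed primary comparison, and a condensed article may leave the choice of method to the full protocol or analysis plan. That silence is not the point here. The point is that the entry rules make the condition very likely to be met, while the only stated power is for the case in which it is not.
- **One third is not a forecast of overlap.** This stands. A reader might infer from Background that the adjusted comparison has power 0.36 to 0.51. The documents do not support that: the figure is AOD service access in an earlier evaluation, not AOD use in this comparison arm. Overlap could be higher, because the target group is described as having both problems and both arms draw referrals from AOD services. It could be lower on the support criterion itself, since all KODY fathers must be Odyssey House clients. AOD is also measured on graded scores (AUDIT and DUDIT), so a yes/no split is a simplification.
- **Baseline scores can restore the loss.** This stands in part. The T1 measures are collected anyway, and with r = 0.5 weighted power passes 0.80 at 67% overlap. So it would be wrong to say that adjusted power falls short in every case. But the sample-size paragraph claims no such gain, and Data analysis does not mention using T1 outcome scores for precision.

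**Conclusion.** The concern holds in a limited form. The 64 + 64 mothers and power 0.80 are correct for an unadjusted t-test and have not been shown to apply to the adjusted comparison that the entry rules make very likely. Without a precision gain from baseline scores, power for d = 0.5 drops below 0.80 once overlap is appreciably under 1: slightly at 80 to 90% (0.71 to 0.78), and heavily at one third (0.36 to 0.51). With the T1 score and weighting, the range at one third is 0.63 (r = 0.5) to 0.79 (r = 0.7), and 0.80 is exceeded at 67% overlap with r = 0.5.

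These figures assume two-sided alpha 0.05, 64 mothers reporting per arm, one yes/no AOD factor to balance, and an overlap and baseline correlation that the documents do not supply. Balancing further covariates would usually lower them. They show the possible size of the loss and do not estimate this trial's power.

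**What to change.** In Recruitment and sampling:
- Keep 128 mothers, and print the alpha and the d behind them.
- Label 0.80 as the power of the unadjusted comparison.
- Add the power of the adjusted comparison over a stated range of overlap and baseline correlation, computed for the analysis that will actually be used. If that analysis includes the T1 score, the printed power should include it too; the r = 0 figures above would then be too low.

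In Data analysis:
- Include the T1 outcome score in the post-group and follow-up comparisons.
- Prefer weighting or score adjustment to 1:1 matching, which loses more power at every overlap below 1.
- Report the effective sample size per arm beside the estimate, so that a null result can be read for what it is.

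The cost is a few sentences and one extra calculation. No more families and no new data are needed. The downside is a less favourable stated power.

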**Methods/Design:**

A quasi-experimental design will be used to assess the primary outcomes of improving the safety and wellbeing of mothers and children whose (ex)partners and fathers respectively participate in KODY (the trial program), when compared with ‘*Caring Dads* standard’ (the comparison group). Psychometric tests will be administered to fathers and mothers at baseline, post-program and at 3-month follow up. Data collection will occur over three years.

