### The intervention

The trial intervention (KODY) is a new model of service that integrates the work of both Kids First and Odyssey House Victoria to address the complex issues for children, women and men living with AOD and DV. The ‘*Caring Dads* standard’ program (the comparison group) consists of the following components.

**Group work**—17 sessions, manualised content, focus on engaging men to examine their fathering, increasing child centred fathering, including respect and support of children’s mothers, and changing patterns of harmful fathering.

**Case Coordination**—case coordination between group intervention and mother contact practitioners.

**Services for mothers and children**—mothers of children with whom fathers have contact are provided support and safety planning through a Child and Family Wellbeing Practitioner.

KODY (the trial program) comprises the ‘*Caring Dads* standard’ program plus the following changes and additions.

**Group work**—‘*Caring Dads* standard’ program with added curriculum materials and specialist AOD facilitation of group sessions.

**Case Coordination**—Collaborative case coordination for fathers by KODY DV and AOD practitioners. Additionally, *Kids in Focus* offers all-of-family case management, which will be integrated with *Caring Dads* case coordination.

**Services for mothers and children**—In addition to support from the Child and Family Wellbeing Practitioner, linked intervention with all family members (children, mothers and fathers) through *Kids in Focus*, including parenting education and support and recreational and therapeutic groups for children and their families.

The intervention group will be implemented by a co-facilitation team with expertise in working with fathers to address DV and AOD. The comparison group will be implemented by professionals experienced in DV and the delivery of *Caring Dads*. Adherence to intervention protocols will be monitored through regular meetings with program staff, recording of participation across time and program components, and observation of selected KODY *Caring Dads* group sessions.

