## Discussion

This paper outlines the protocol for a quasi-experimental trial of the innovative KODY program, an all-of-family response to co-occurring issues of DV and AOD. A quasi-experimental design was deemed most appropriate for the trial, as randomized allocation to trial and comparison groups is impracticable and potentially unethical in the context of the program and the service system in which it operates. Primary outcomes for the study are the increased safety and wellbeing of mothers and children whose (ex)partners and fathers respectively participate in KODY (the trial program), when compared with ‘*Caring Dads* standard’ (the comparison group).

Through an analysis of both outcomes measures and file reviews to provide ‘dose’ level information, the study aims to build the evidence for program responses that increase the safety and wellbeing of women and children impacted by men who use DV and AOD. The innovative aspects of the program—addressing the co-occurrence of DV and AOD with a specific focus on fathering, providing support to all members of the family and centring the needs of children—are all drawn from both academic evidence and practitioner expertise. The innovative nature of the program may result in small sample sizes in the early years of implementation, which may limit the power of analyses, but the authors’ experience with the evaluation of other innovative programs suggests that sample sizes will increase with program longevity. Operating within the DV and AOD service sectors respectively, the two partner organisations—Kids First and Odyssey House Victoria—have a shared focus on the needs of vulnerable children and train their staff in a common framework (Safe and Together) which brings a shared language and conceptualisation of the intersection of AOD and DV [30]. In the study context of Victoria, Australia, their joint commitment to collaborating across these sectors exemplifies a shift in the service system context and policy drivers away from a siloed service system which results in separate and disconnected service responses, particularly when children are involved [21].

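### The 170-family target gives 128 mothers and power 0.80 only if no contacted mother is lost by T2/T3 and contact reaches 75% in the comparison arm, where the stated reason for 75% does not apply

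*Protocol article*

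**What the plan says.** The sample size is set out in the protocol article under Recruitment and sampling. It assumes a medium standardised effect, "a power of 0.80 and a two-tailed test across independent groups", and concludes that "this study will need to involve reports from 128 mothers, 64 in each of the KODY and comparison groups". It then cites participation rates of 62% to 97% from earlier Caring Dads evaluations. The rate it adopts is introduced with the words "Assuming a partner contact success rate of 75% based on the benefits of the", and the service named as the reason is Kids in Focus. From that rate it derives the target: "this study will need to enrol 170 families across groups". The same section plans three KODY and three comparison groups in each study year, with up to 10 participants per group.

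Four other parts of the article bear on this:

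- **The intervention** lists Kids in Focus among the additions that make up KODY: "linked intervention with all family members (children, mothers and fathers) through" that program. The comparison program gives mothers a Child and Family Wellbeing Practitioner, which KODY mothers also receive. **Eligibility criteria** likewise places the Kids in Focus offer in the intervention group.
- **Data collection** has mothers completing measures at T1, T2 and T3, the last three months after the program ends. Recruitment and sampling says consent is confirmed again at each stage.
- The **Abstract** fixes the period: "Data collection will occur over three years".
- The **Discussion** accepts that early samples may be small and may limit power, but expects that "sample sizes will increase with program longevity".

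**The concern.** Two things are wrong with how 170 is built.

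First, reaching a mother is not the same as having her outcome at T2 or T3. The requirement is for reports from 128 mothers, and the step from 128 to 170 pays only for failure to contact. The women's primary measure, the Composite Abuse Scale, is completed by mothers, so a mother who stops responding has no observed value, whatever analysis set is used.

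Second, the reason given for 75% is a service that the comparison arm is not described as receiving, yet half of the 128 reports must come from that arm.

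The planned group capacity leaves little room to recover a shortfall. At stake is how a null or imprecise result on women's safety is read. A reader who takes the 0.80 at face value could treat it as fair evidence of no added benefit from KODY, although the power actually available may have been lower.

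**Working it through.** **Inputs.** From Recruitment and sampling: power 0.80, two-tailed, independent groups, 64 mothers per group, 75% contact, cited range 62% to 97%, 170 families, three groups per arm per year of up to 10. From the Abstract: three years. The article prints neither the value of d nor alpha; I take d = 0.5 and two-sided alpha 0.05. It gives no loss rate for mothers, so 5% to 30% is shown as an assumed range.

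**1. The plan's own figure.** A two-sample t-test at these values needs 63.8, so 64 per group, with power 0.801. This reproduces the plan and supports the two assumed inputs. Inflation: 128 / 0.75 = 170.7. Back-check: 170 x 0.75 = 127.5 mothers, power 0.80. The figure is right on its own terms, and its only inflation is for contact.

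**2. Capacity.** (3 + 3) groups x 10 places x 3 years = 180 at most. The target uses 170 / 180 = 94% of all places.

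**3. Adding loss by T2/T3.** Analysable mothers = families x 0.75 x (1 - loss), split equally; power from the t-test.

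| Loss (assumed) | 170 families: mothers | Power | 180 families: mothers | Power |
|---|---|---|---|---|
| 0% | 127.5 | 0.80 | 135.0 | 0.82 |
| 5% | 121.1 | 0.78 | 128.2 | 0.80 |
| 10% | 114.8 | 0.76 | 121.5 | 0.78 |
| 20% | 102.0 | 0.71 | 108.0 | 0.73 |
| 30% | 89.2 | 0.65 | 94.5 | 0.67 |

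**4. Largest loss that full capacity can absorb at 75% contact.** 1 - 128 / (180 x 0.75) = 1 - 128 / 135 = 5.2%. To keep 128 mothers, 10% loss needs 128 / (0.75 x 0.90) = 189.6, so 190 families; 20% loss needs 128 / (0.75 x 0.80) = 213.3, so 214. Both exceed 180.

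**5. Lower contact in the comparison arm only.** With 85 families per arm, KODY at 75% and comparison at the cited low of 62%: 85 x 0.75 = 63.75 and 85 x 0.62 = 52.7 mothers, power 0.76 before any loss. With all 180 places: 67.5 and 55.8, power 0.78.

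**6. The other end of the cited range.** At 97% contact in both arms, 170 x 0.97 = 164.9 mothers, and 1 - 128 / 164.9 = 22% loss can be absorbed. At 180 families: 174.6 mothers and 27%.

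**7. Detectable effect at power 0.80.** About d = 0.53 with 57 mothers per arm (170 families, 10% loss) and about 0.60 with 45 per arm (30% loss).

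**The case against.** The strongest reply is that the plan's figures are correct on its own inputs. 170 families at 75% give 127.5 mothers and power 0.80, and the gap between 170 and 171 is rounding. The article gives no attrition rate and no arm-specific contact rate, so a shortfall is not shown. This stands. A reader might infer that 128 mothers and power 0.80 will not be reached; the documents do not support that, because it depends on rates they do not give.

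The 75% is also not an aggressive value. It lies below the midpoint of the cited range (79.5%), at which 180 places would absorb 1 - 128 / (180 x 0.795) = 10.5% loss. Comparison mothers have their own practitioner, so 62% in that arm is a worst case. That stands as to the value, but not as to the reason: the article rests the rate on a service it describes only for KODY. The 75% might have been meant to cover participation through to the final report, since the preceding sentence speaks of participation rates, but it is called a contact rate and nothing says it extends to T3.

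The sentence on premature drop-out in Data analysis concerns participation in the program and who stays in the intent-to-treat analysis. It does not forecast missing reports from mothers, and I do not use it so. An honorarium at each data collection point should help retention, but no retention figure follows from it.

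Baseline adjustment could recover power. With 51 per arm it would be about 0.75 at a baseline correlation of 0.3 and 0.82 at 0.5. The article does not specify such an adjustment, and the stated calculation does not use one.

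A reader might also see the Discussion's expectation of growing samples as contradicting the 180-place ceiling. It does not: groups are of up to 10, so they can start small and fill later. Nor do the documents support a claim that the last groups miss T3 within three years, since session frequency and start dates are not given, or any specific loss of power from clustering, since no intraclass correlation is given.

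**Conclusion.** The point holds in conditional form. The stated 0.80 at 170 families requires both that every contacted mother reports at T2/T3 and that the comparison arm reaches 75% contact. The article makes no allowance for the first, and its reason for the second applies only to KODY. Capacity offers little reserve: at 75% contact, even all 180 places tolerate only about 5% loss.

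At 170 families and 75% contact, power is about 0.76 with 10% loss and 0.71 with 20%. It is about 0.76 with no loss if comparison contact is 62%. If contact approached 97%, more than 20% loss could be absorbed.

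These powers rest on d = 0.5, two-sided alpha 0.05, an unadjusted two-sample t-test and assumed loss rates. The first two reproduce the plan's 64 per group. The paragraph should be corrected, but the design is not shown to fail.

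**What to change.** Rewrite the sample-size paragraph under Recruitment and sampling so that it:

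- gives a contact rate for each arm, each justified by services which that arm receives;
- adds an explicit retention allowance to T3 or, if 75% was meant to cover contact through to the final report, says so and gives the basis;
- reports expected analysable mothers per arm as places filled x contact x retention, within the 180-place ceiling;
- replaces the unqualified 0.80 with power and detectable d over a stated range, for example about 0.53 at 57 per arm to 0.60 at 45 per arm.

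The cost is one rewritten paragraph and a less favourable stated power. No extra enrolment and no change to the groups is needed.
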